### Secondary Objectives

#### *Adherence*

Attendance at each planned CRM visit will be recorded. An opportunity will be offered to make-up missed visits within one week of the due date – attendance at a make-up visit would count towards adherence for that week. The reasons provided for missed visits will be recorded. Adherence will be reported as proportion of planned weekly attended for each patient.

The total number of planned weekly visits will be 12 for all participants except those who discontinue the study intervention early due to death, transfer of care or permanent catheter removal. The number of planned visits will be capped at discontinuation date for these participants. For the purpose of the adherence analysis, participants who discontinue the study intervention early due to parent or clinician request will be assumed to have 12 planned visits.

#### *Correlation between CRM results and catheter occlusion or dysfunction*

At each weekly visit, information will be collected about worst line function in the past week. Data will be collected throughout the study for use of thrombolytic agents. Events will be confirmed where possible by examination of the medical record or direct contact with treating clinicians.

The relationship between CRM measurements and subsequent occlusion or dysfunction will be explored graphically.

All occlusion or dysfunction events which are managed with thrombolytic agents, or lead to long-term modification of CVAD use or CVAD removal, will be counted towards catheter occlusion or dysfunction. The type of event (total, aspiration or flush occlusion or dysfunction) will be determined by study staff after consultation with the treating clinical team.

### **Exploratory Objectives**

#### *Acceptability*

Measurement of acceptability for medical interventions other than medication is not well standardized. [Atkinson, 2005]

Some investigators have used study retention and adherence as a surrogate of acceptability, but this has limitations. Although acceptability would be expected to partially predict attrition or non-adherence, perfect adherence does not necessarily represent perfect acceptability, especially in a highly motivated population with institutional loyalty such as leukemia patients at St Jude. In this population, families might even comply with an intervention which they find objectionable. Similarly, adherence with an acceptable intervention can be poor because of many factors unrelated to

acceptability. Other investigators have used questionnaires to assess acceptability, but there is currently no well-validated instrument.

A custom-built 10 item acceptability questionnaire focused on relevant domains of 'acceptability' will be used as the primary measure of this construct. A 6 point forced-choice Likert-type scale will be used for each item. (Appendix II)

The acceptability questionnaire will be administered at 4, 5, 11 and 12 weeks. The questionnaire will be completed at each time point by either the caregiver, or the participant if over 18 years of age. The completed questionnaires will be placed in a sealed opaque envelope and scored by a person other than the PI to encourage frank responses. Participants who discontinue the study intervention early will complete an acceptability questionnaire at time of exit from the study if possible, but will not complete further questionnaires after that time.

The proposed domains (subscales) of acceptability are; time-cost (Questions 1, 4 and 7), worry or anxiety (Questions 2, 5 and 8) and adverse effects (Questions 3, 6 and 9). There will also be a single item assessing 'overall acceptability' (Question 10).

Although the perception of necessity and efficacy are likely to be important correlates of acceptability of an intervention, it is incongruous to test these in the context of a study which provides no potential benefit to participants.

Scoring of the questionnaire will be performed as follows: Subscale scores will be determined by summing the scores for each item (1 - 6 points per item). Unanswered items will be excluded. The total acceptability score will then be determined by summing the score for each of the acceptability subscales plus three times the overall acceptability score and expressing this as a percentage of the maximum possible score for answered items.

Validity of the questionnaire will be assessed during the study by measuring reproducibility, convergent validity and predictive validity using simple regression analysis.

Predictive validity of the questionnaire will be determined by correlation between acceptability scores and adherence to subsequent study visits. Although not all non-adherence is related to non-acceptability, it would be expected that a correlation would exist if the questionnaire truly measures this construct.

Data will be collected throughout the study for diagnosis of bloodstream infection, intravascular thrombosis or pulmonary embolism. Events will be

confirmed where possible by examination of the medical record or direct contact with treating clinicians.

Radiology, microbiology and pharmacy records will be searched for confirmatory information about thrombosis, positive blood cultures and thrombolytic agent use. Information will be sought from affiliate hospitals and other sites for events which are reported to have occurred elsewhere.

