### **5.2 Evaluations During Study**

Catheter resistance will be measured weekly during the study period as described in Section 4.3.

Data will be collected for catheter-related complications throughout the study period, until 21 days after the last CRM visit, as described in Section 4.5.

At weeks 4, 5, 11, and 12 (+/- 1 week) caregivers (or participants over the age of 18) will complete a questionnaire regarding acceptability of the CRM procedure. [Appendix II]

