### **9.3 Analysis for Exploratory Objectives**

#### **9.3.1 To assess acceptability of weekly CRM for participants and caregivers**

To assess acceptability over the entire study period, mean acceptability scores for each participant from all timepoints will be calculated and described. To assess change in acceptability over the study period, mean acceptability scores for all patients at each timepoint will also be calculated and described.

The test-retest reliability of the acceptability questionnaire will be assessed using the intra-class correlation for each subscale and the overall acceptability score for questionnaires completed one week apart.

Predictive validity of the acceptability questionnaire will be explored using a logistic regression model to assess whether higher acceptability scores are associated with adherence at subsequent planned visits.

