### Catheter Resistance Testing Questionnaire (Parent version)

Thank you for completing this short questionnaire about catheter resistance testing. There are 10 questions.

To answer each question, think about **the last two times** you had catheter resistance testing done.

You can leave comments if you want to.

Your answers will be placed in a sealed envelope and entered directly into a computer database by a staff member who is not directly involved in catheter resistance testing

1. Catheter resistance testing took up too much of my time

☐  
Strongly  
Disagree

☐  
Disagree

☐  
Somewhat  
Disagree

☐  
Somewhat  
Agree

☐  
Agree

☐  
Strongly  
Agree

Comments:

2. My child appeared nervous or worried (e.g. fidgety, sweaty palms) before catheter resistance testing

☐  
Strongly  
Disagree

☐  
Disagree

☐  
Somewhat  
Disagree

☐  
Somewhat  
Agree

☐  
Agree

☐  
Strongly  
Agree

Comments:

3. My child had side-effects from catheter resistance testing

☐  
Strongly  
Disagree

☐  
Disagree

☐  
Somewhat  
Disagree

☐  
Somewhat  
Agree

☐  
Agree

☐  
Strongly  
Agree

Comments:

4. Catheter resistance testing interfered with other activities

☐  
Strongly  
Disagree

☐  
Disagree

☐  
Somewhat  
Disagree

☐  
Somewhat  
Agree

☐  
Agree

☐  
Strongly  
Agree

Comments:

5. My child was calm during catheter resistance testing

|                       |                       |                       |                       |                       |                       |
|-----------------------|-----------------------|-----------------------|-----------------------|-----------------------|-----------------------|
|  |  |  |  |  |  |
| Strongly
Disagree  | Disagree              | Somewhat
Disagree  | Somewhat
Agree     | Agree                 | Strongly
Agree     |

Comments:

6. Catheter resistance testing was uncomfortable or painful

|                       |                       |                       |                       |                       |                       |
|-----------------------|-----------------------|-----------------------|-----------------------|-----------------------|-----------------------|
|  |  |  |  |  |  |

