| Strongly
Disagree  | Disagree              | Somewhat
Disagree  | Somewhat
Agree     | Agree                 | Strongly
Agree     |

Comments:

7. Catheter resistance testing was easy to fit into my week

|                       |                       |                       |                       |                       |                       |
|-----------------------|-----------------------|-----------------------|-----------------------|-----------------------|-----------------------|
|  |  |  |  |  |  |
| Strongly
Disagree  | Disagree              | Somewhat
Disagree  | Somewhat
Agree     | Agree                 | Strongly
Agree     |

Comments:

8. Catheter resistance testing seemed stressful for my child

|                       |                       |                       |                       |                       |                       |
|-----------------------|-----------------------|-----------------------|-----------------------|-----------------------|-----------------------|
|  |  |  |  |  |  |
| Strongly
Disagree  | Disagree              | Somewhat
Disagree  | Somewhat
Agree     | Agree                 | Strongly
Agree     |

Comments:

9. My child didn't like the way catheter resistance testing felt

|                       |                       |                       |                       |                       |                       |
|-----------------------|-----------------------|-----------------------|-----------------------|-----------------------|-----------------------|
|  |  |  |  |  |  |
| Strongly
Disagree  | Disagree              | Somewhat
Disagree  | Somewhat
Agree     | Agree                 | Strongly
Agree     |

Comments:

10. Overall, catheter resistance testing is acceptable to me

|                       |                       |                       |                       |                       |                       |
|-----------------------|-----------------------|-----------------------|-----------------------|-----------------------|-----------------------|

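### Minor: the questionnaire's test-retest ICC does not hold the caregiver fixed within a one-week pair, and as worded it leaves out the total acceptability score

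*Protocol*

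**What the plan says.** Section 4.5 (Acceptability) gives the respondent rule: "The questionnaire will be completed at each time point by either the caregiver, or the participant if over 18 years of age". Section 5.2 repeats it in the plural: "At weeks 4, 5, 11, and 12 (+/- 1 week) caregivers (or participants over the age of 18) will complete a questionnaire". Neither names a designated caregiver or asks that one person complete consecutive forms.

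Appendix IV reproduces a parent version and a participant version. Each has ten items with comment lines. Neither has a field for which caregiver answered. The form tells the respondent: "Your answers will be placed in a sealed envelope and entered directly into a computer database by a staff member", and that this staff member is not directly involved in the testing.

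Section 9.3.1 plans the "intra-class correlation for each subscale and the overall acceptability score for questionnaires completed one week apart".

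Section 4.5 uses two different names for scores. *Overall acceptability* is a single item, Question 10. The *total acceptability score* is the sum of the three subscales "plus three times the overall acceptability score", expressed as a percentage of the maximum for answered items.

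**The concern.** A test-retest ICC needs the same person to answer twice. If two caregivers of one child complete the two forms of a pair, real differences between them are counted as instrument error.

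The parent form is open to this. Items 1, 7 and 10 ask about the respondent's own time, own week and own view of acceptability, so two parents can both answer correctly and differ. Other items are proxy judgements of the child, for example "Catheter resistance testing seemed stressful for my child", which two observers may rate differently.

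The second part concerns which scores get a reliability estimate. Section 4.5 says that no well-validated instrument exists and makes this questionnaire the main measure of acceptability, with reproducibility to be assessed during the study. On the protocol's own definitions, the list in 9.3.1 covers three subscales and one item but not the composite built from them.

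**Working it through.** The protocol gives no target ICC, precision or power for this analysis, so there is no planned figure to reproduce.

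**Score structure (section 4.5).** Each item scores 1–6 and each subscale has three items.
- Maximum total = 3 × (3 × 6) + 3 × 6 = 54 + 18 = 72.
- Question 10 contributes 18/72 = 25%. It is not the total.
- Items 1, 7 and tripled Question 10, which ask about the respondent personally, contribute (6 + 6 + 18)/72 = 30/72, or about 42% of the maximum.

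**Effect of a changed caregiver.** Let *s* be the share of one-week pairs with different caregivers. Then approximately

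expected ICC = (1 − *s*) × ICC(same person) + *s* × ICC(between caregivers).

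All inputs are assumptions, because the protocol gives none. With ICC(same person) = 0.80:

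| ICC between caregivers | *s* = 10% | *s* = 25% | *s* = 50% |
|---|---|---|---|
| 0.7 | 0.79 | 0.775 | 0.75 |
| 0.6 | 0.78 | 0.75 | 0.70 |
| 0.4 | 0.76 | 0.70 | 0.60 |

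For example, with 0.4 and 25%: 0.75 × 0.80 + 0.25 × 0.4 = 0.60 + 0.10 = 0.70.

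**Against sampling error.** A simulation with a one-way ICC, one pair for each of 35 participants and 3,000 runs per setting gave a 2.5–97.5% range of about 0.63–0.89 with no switching. Eight of the nine expected values in the table lie inside that range. Only 0.60 lies below it.

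**Can the total's ICC be read off the listed ICCs?** For a sum of components, the ICC is the summed true-score covariance divided by the summed true-score plus error covariance. Assume equal component SDs, subscale ICCs of 0.7 and a Question 10 ICC of 0.6. Scale each component variance to 1.
- True-score correlation 0.2, error correlation 0.3: true sum = 2.7 + 6 × 0.7 × 0.2 + 6 × √0.42 × 0.2 = 4.32; error sum = 1.3 + 6 × 0.3 × 0.3 + 6 × √0.12 × 0.3 = 2.46; ICC = 4.32/6.78 = 0.64.
- True-score correlation 0.8, error correlation 0: true sum = 2.7 + 6 × 0.7 × 0.8 + 6 × √0.42 × 0.8 = 9.17; error sum = 1.3; ICC = 9.17/10.47 = 0.88.

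The same component ICCs are compatible with anything from about 0.64 to 0.88 for the total, so its reliability has to be estimated directly.

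**The case against.** Much of the case on the other side stands.

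- **The respondent may be recorded elsewhere.** A reader might infer that mixed pairs can never be found afterwards. The reproduced forms also show no study number, date or week, and these must be captured somewhere or no forms could be paired. A case report form not shown could hold the respondent too. The documents show only that the form itself does not record it.
- **Turning 18.** A reader might count participants who move to the other version as hidden mixed pairs. They are not hidden, because the version identifies them. They are also rare. If entry ages are uniform over 5 to under 25 (20 years, about 1,040 weeks), the two one-week gaps cover 2/1,040 ≈ 0.2% per participant, or about 0.07 of 35.
- **Alternation over 12 weeks.** Only a switch inside a one-week pair affects the ICC. Section 4.5 speaks of the caregiver in the singular and may intend one person, though it does not say so. The documents give no switching rate.
- **A sound instrument would look unreliable.** The inputs do not support this as an expectation. It needs frequent switching together with low agreement between caregivers.
- **The total score.** In 9.3.1 the authors may have meant the total when they wrote overall. A reader might also say that the reported score has no reliability estimate. Section 9.3.1 reports mean acceptability scores without the word total, so that is a reasonable inference but not something the protocol states. The total's ICC can also be computed later from the stored items.

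The respondent's identity is different. If it is not captured at the time, no later analysis plan can recover it.

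**Conclusion.** The point holds as a minor one within an exploratory objective. No primary or secondary result depends on it, and no decision rule is attached to the ICC.

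Two things are established from the text. Sections 4.5 and 5.2 do not hold the caregiver fixed within a pair, and the forms do not show which caregiver answered. As worded, 9.3.1 omits the total acceptability score.

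The size of the first is unknown. On the assumptions above (same-person ICC 0.80, agreement between caregivers 0.4–0.7), the expected loss is 0.01–0.04 with 10% of pairs mixed, 0.025–0.10 with 25%, and 0.05–0.20 with 50%. Most of this lies within sampling error at 35 participants, although it always pushes the ICC down. The second is a gap in wording, with no loss of data.

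**What to change.** - **Section 4.5:** ask that the same person complete both forms of a pair (weeks 4/5 and weeks 11/12) where possible. Record who answered, by a tick box on the form or an entry on the case report form.
- **Section 9.3.1:** compute the main test-retest ICC from same-respondent pairs, with all pairs as a sensitivity analysis. Name the scores as each subscale, Question 10 and the total acceptability score.

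The cost is one recorded field and a few sentences, with no change to visits, procedures or sample size. A few mixed-respondent pairs would leave the main ICC, which matters a little with at most 35 participants. A tick box also makes a form meant to encourage frank answers slightly more identifying. Recording the respondent on the case report form instead keeps it off the questionnaire.

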## **4.0 DESIGN AND METHODS**

### **4.1 Design and Study Overview**

The trial will be a single-group prospective study of weekly catheter resistance monitoring for 12 weeks.

Participants will be enrolled at any point during treatment.

The study aims to recruit 35 evaluable participants. Based on estimates by representatives of each hospital team, approximately 80 patients per year would be eligible for enrollment (Bone marrow transplant, 40; Leukemia, 10; Neurooncology, 15; Solid tumor, 15).

During the study period, participants will be monitored for CVAD related complications, adherence to CRM visits and participant/caregiver satisfaction.

Participants who receive thrombolytic therapy to restore CVAD patency, or whose CVAD is removed and replaced with another eligible tunneled CVAD will remain on study. The next CRM reading will act as a new baseline for each lumen.

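### Acceptability subscales are unscaled sums, so a blank item counts as 0 on a 1–6 item and distorts the planned subscale test-retest ICCs (minor; total score unaffected)

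*Protocol*

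**What the plan says.** The acceptability part of protocol section 4.5 sets out a ten-item questionnaire. Nine items form three subscales of three items each (time-cost, worry or anxiety, adverse effects), and Question 10 is a single overall item. On the response format it says "A 6 point forced-choice Likert-type scale will be used for each item".

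The subscale rule is: "Subscale scores will be determined by summing the scores for each item (1 - 6 points per item). Unanswered items will be excluded". The next sentence builds the total from the three subscale scores plus three times the overall item, and finishes by "expressing this as a percentage of the maximum possible score for answered items". That rescaling is attached to the total. No passage rescales a subscale or sets a minimum number of answered items for one.

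Section 9.3.1 plans to assess test-retest reliability "using the intra-class correlation for each subscale and the overall acceptability score for questionnaires completed one week apart". On timing, section 4.5 says "The acceptability questionnaire will be administered at 4, 5, 11 and 12 weeks", which gives two one-week pairs per participant (4/5 and 11/12). On means, 9.3.1 says "mean acceptability scores for each participant from all timepoints will be calculated and described", and it plans the same for all patients at each timepoint. It does not mention subscale means.

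**The concern.** Leaving an item out of a plain sum is the same as scoring it 0, and 0 is not an available answer on a 1–6 item. A family whose view has not changed, but which leaves one box empty on the second form, shows a large apparent change on that subscale. Test-retest ICCs treat such changes as measurement error.

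The protocol says that no well-validated instrument exists and makes this custom questionnaire its primary measure of acceptability. The subscale ICCs are part of the planned evidence that it is reproducible. A few blanks could make a reproducible subscale look unreliable because of the scoring rule alone. The protocol anticipates blanks, since it writes a rule for them.

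**Working it through.** The protocol gives no numerical result on this point, so there is no figure to reproduce. The check applies the written rule first and then simulates its effect on the ICC.

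**Inputs from the protocol.** Three items per subscale, each scored 1–6; sum of answered items; total rescaled to answered items (all section 4.5). ICC per subscale for forms one week apart (9.3.1). Sample size: "The study aims to recruit 35 evaluable participants" (4.1), so at most 35 pairs per one-week interval, or 70 if both intervals are pooled.

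**Step 1. Subscale, written rule.** Score = sum of answered items; a complete subscale runs from 3 to 18.
- 5, 5, 5: 15. With one blank: 5 + 5 = 10, a fall of 5/15 = 33%.
- 6, 6, 6: 18. With one blank: 12.
- 4, 4, 4: 12. With one blank: 8.

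**Step 2. Subscale, prorated.** Score = 3 × mean of answered items. For 5, 5, blank: 3 × (10/2) = 15, equal to the complete score.

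**Step 3. Total score.** Total = 100 × (sum of answered subscale items + 3 × Q10) / (6 × number of subscale items answered + 18), when Q10 is answered. With all answers 5:
- complete: 100 × (45 + 15)/(54 + 18) = 100 × 60/72 = 83.3%;
- one blank among the nine: 100 × (40 + 15)/(48 + 18) = 100 × 55/66 = 83.3%.

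The total is protected; the subscales are not.

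**Step 4. Effect on the ICC.** Assumed, because the protocol gives none of it: item answer = item mean + person effect + stable person-by-item effect + occasion error, rounded and limited to 1–6; items skipped independently at random; one-way ICC of two forms. SDs are listed as person / person-by-item / occasion.

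| SDs; item mean | Complete | Rule | 1% skipped | 2% | 5% | 10% |
|---|---|---|---|---|---|---|
| 0.8/0.5/0.5; 4.8 | 0.86 | raw sum | 0.77 | 0.69 | 0.53 | 0.37 |
| 0.8/0.5/0.5; 4.8 | 0.86 | prorated | 0.85 | 0.85 | 0.84 | 0.82 |
| 0.8/0.5/0.5; 2.2 | 0.86 | raw sum | 0.83 | 0.81 | 0.74 | 0.64 |
| 0.9/0.5/0.6; 5 | 0.841 | raw sum | 0.754 | 0.682 | 0.523 | 0.368 |
| 0.9/0.5/0.6; 5 | 0.841 | prorated | 0.838 | 0.835 | 0.824 | 0.807 |
| 0.9/0.5/0.6; 4 | 0.854 | raw sum | 0.806 | 0.760 | 0.649 | 0.512 |

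**Step 5. At the planned size.** One subscale ICC from 35 pairs rests on 35 × 2 × 3 = 210 item responses. With SDs 0.9/0.5/0.6 and item mean 5, one blank lowers the average ICC from 0.83 to 0.79, and three blanks lower it to 0.71. With SDs 0.8/0.5/0.5 and item mean 4.8, two blanks (2/210, about 1%) lower it from 0.85 to 0.76. Pooling both intervals would dilute the same number of blanks.

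**The case against.** The strongest reply is that this is a narrow drafting gap in an exploratory objective, and that its size is not known. Most of that stands.

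- **The acceptability result.** A reader might infer that the reported acceptability level is biased. It is not: the total is rescaled to answered items, and the planned means are most naturally read as means of that total.
- **Subscale means.** A reader might also infer that subscale means are pulled down. They would be if they were reported, but no passage plans them, so this is not part of the point.
- **Size depends on item level.** A blank costs more where scores are high. Seven of the nine subscale items are worded negatively (Questions 1, 2, 3, 4, 6, 8 and 9). If strong disagreement were scored 1, a satisfied family would score low on them and a blank would cost 1–2 points rather than 5. The item-mean-2.2 row shows this milder case.
- **Spread.** It is tempting to say that one blank outweighs the differences between families. The documents give no spread, and at item mean 2.2 a blank costs about 2.3 points against a simulated subscale SD of about 2.5, so the statement cannot be made in general.
- **Skip rate.** Ten single-tick items may produce few blanks. At 0.5% skipped with item mean 4.8, the ICC is about 0.81 against 0.86.

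What does not stand is that an analyst would prorate anyway. The written rule is to sum and exclude, so prorating would depart from it. Nor does the forced-choice format remove the problem, because the protocol itself provides for unanswered items.

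**Conclusion.** The rule is wrong as written, but the matter is minor. Followed literally, section 4.5 scores a blank as 0 on a 1–6 item within a subscale, and 9.3.1 carries that score into three planned test-retest ICCs. That part is arithmetic and needs no assumption.

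The size does rest on assumptions. With person, person-by-item and occasion SDs of 0.8, 0.5 and 0.5 and item means between 2.2 and 4.8, the raw-sum ICC is about 0.77–0.83 at 1% skipped, 0.69–0.81 at 2% and 0.53–0.74 at 5%. The complete-data value is about 0.86 and the prorated value about 0.84–0.85. The second set of SDs shows the same pattern. The downward direction holds across all the cases run, but it presumes blanks scattered at random; a family that leaves the same item blank on both forms would not produce a spurious change between them.

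The documents do not support a wider claim. The harm is confined to the subscale ICCs and arises only if items are skipped.

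**What to change.** In section 4.5, state that each subscale score, like the total, is the sum of its answered items as a percentage of six times the number answered. Three times the mean of the answered items is equivalent: it is the same score on the 3–18 scale and gives the same ICC. State in 9.3.1 that the subscale ICCs use this score.

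This takes one sentence in 4.5 and a cross-reference, with no new data and no change to the questionnaire. Requiring at least two of the three items to be answered is an optional addition. The total has no such threshold, and the small cost is that a subscale with two or more blanks becomes missing and its pair drops out of that ICC.
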